### Measures

#### Autonomic Nervous System (ANS) Activation

Measures of ANS activation include parameters that are either directly measured or that can be derived from primary signals. Thus, measures of systolic and diastolic blood pressure and mean arterial pressure are obtained as well as heart rate, cardiac output, total peripheral resistance, pre-ejection period, and heart rate variability. Cardiac and hemodynamic measures are recorded noninvasively according to established guidelines for impedance cardiography and blood pressure measurement [109]. Condition averages of the cardiac and hemodynamic measures are derived from the electrocardiogram (ECG) and blood pressure monitor. For each measure, scores from the baseline condition will be compared with task condition scores to indicate reactivity [110]. Vagal control is assessed via respiratory sinus arrhythmia (RSA) which will be derived from both ECG recordings and respiration estimated from impedance waveforms (ZKG). A computer program (Mindware) is used to identify R spikes and R-R intervals in the ECG waveform with inaccurately identified R spikes manually corrected. The data are detrended and submitted to Fast Fourier Transformation, and the high-frequency power spectrum (0.15-0.40Hz) is used as an index of RSA [111]. Because we are studying a healthy population and reactivity is not a clinical endpoint, we will consider whether patterned responses during and after the task are consistent with a maladaptive vs. an adaptive response. Following Porges' work we will interpret greater vagal control as a more adaptive regulatory response. While statistical and clinical significance may not be the same, statistically significant effects in these experiments would provide important evidence of an underlying biological mechanism for the beneficial effects of social interactions and the role of oxytocin in this process.

#### Hormone Measures

Salivary hormone concentrations reflect the unbound serum hormone fraction and are considered a reliable and valid measure of the free fraction concentration of the hormone in the blood [112,113]. Saliva samples are collected using IBL sampling devices and the methodology described by Kirschbaum and Hellhammer [114]. Four saliva samples are collected from each participant over the course of the experimental session. After participants expectorate 1 ml of saliva into the Sali-caps, each saliva sample is stored (in -80 degrees C) until required for biochemical analysis, when they are sent to a laboratory to be assayed. A random sample of 20% of the samples will be assayed in duplicate. Anabolic balance will be derived from assay results by creating a ratio of DHEA/cortisol after molar transformation to equate unit values [107]. Estrogen is measured using estradiol obtained from the first saliva sample taken at the laboratory session [113,115].

### Equipment

The psychophysiology laboratory at HSPH includes equipment for assessing cardiovascular function within a four-room suite that includes a control room and rooms for collecting physiological and other types of data. It is equipped with a Biopac MP150 system (BIOPAC Systems Inc, Goleta, CA) for the measurement of ECG, impedance cardiography, and blood pressure. It is further equipped with a stadiometer, stimulus presentation equipment, and a complete audio-visual system for monitoring and data collection (including multiple video cameras, speakers, etc). The laboratory also has capacity for extraction and storage of biological samples (e.g., blood, urine, saliva). Blood pressure is recorded with a Medwave blood pressure monitor that provides continual readings of blood pressure. Cardiac responses are obtained with ECG system using a Standard lead II configuration (ECG100C) and an impedance cardiograph system (NICO100C). The impedance cardiograph uses a four mylar band configuration placed around the neck and torso and was developed according to published guidelines [125]. All signals are conditioned, amplified, and recorded onto a computer for subsequent editing and ensembling. The editing program (Mindware Suite, Mindware Technologies, Westerville, OH), is a specialized scoring program that allows for artifact editing and ensembling averages of impedance waveforms.

### Data Analyses

Analysis will begin with thorough descriptive and graphical examinations of variables in both studies, including comparisons across randomization groups. Analyses will include adjustment for covariates if not covered by randomization. Distributional assumptions of dependent variables will be assessed, and measures will be transformed, if necessary. Analyses will use applications of the general linear model as appropriate for each hypothesis under study. For example, when examining relations between the dichotomous factors of social support, oxytocin, and gender, we will use analyses of variance (ANOVA) with repeated measures. Responses are measured over time both before and after the stress induction. Cardiovascular outcomes will be considered both in separate models and using multivariate analysis of variance, as they are likely correlated within each individual. When considering the relation between age (a continuous factor) and oxytocin, we will use multiple linear regression techniques incorporating an interaction term between age and oxytocin as well as relevant covariates, but we will also consider using linear mixed models to account for the repeated measures on the outcomes and the resulting intra-individual correlation in these measures. Statistical tests will be two-tailed and conducted at the .05 level of significance. Regarding the specific hypotheses, this experimental study provides data for analyses that will examine whether:

1) Under conditions of stress, higher levels of oxytocin lead to higher vagal control, more benign stress reactivity (reduced blood pressures, cardiovascular response patterns characterized by increased ventricular contractility, heart rate, and cardiac output, but decreased total peripheral resistance), higher anabolic balance, and reduced subjective distress, by comparing the change in responses before and after stress across the oxytocin and placebo control groups.

2) Oxytocin combined with social support reduces the effects of stress more than the individual effects of oxytocin and social support by comparing the change in responses before and after stress across all possible combinations of the two treatment groups (oxytocin vs. placebo; social support vs. no social support). Oxytocin and social support combined is expected to be associated with highest levels of vagal control, the most benign pattern of autonomic reactivity, and the lowest levels of subjective distress.

3) Oxytocin reduces effects of stress more for women than for men by comparing changes in responses before and after stress in the presence of oxytocin or placebo across men and women. Exploratory analyses will consider whether the strength of the effects of oxytocin may be attributable to differences in estrogen levels by comparing effects of oxytocin across pre- and post-menopausal women (estrogen levels are expected to be higher among pre-menopausal women) and also considering interactions between estrogen (measured directly via levels of estradiol) and oxytocin in both men and women.

4) Effects of oxytocin are similar across younger and older aged adults by comparing the change in responses before and after stress in the presence of oxytocin or placebo across age.

The general analytic strategy will start by fitting a model that includes all interactions and then move to a statistically equivalent simpler model using likelihood ratio tests. In cases where there are more than two measurements over time, several covariance structures will be considered. The possibility of multiplicative effects (between oxytocin and social support, for instance) will be explored graphically. Other research has suggested that the effects of oxytocin and/or social support may not emerge immediately. Thus, elapsed time will be an important consideration, and separate analyses will be conducted to determine when over the course of the experimental tasks, effects of oxytocin and/or social support are evident on cardiovascular, neuroendocrine, and subjective parameters. These analyses will involve multiple single comparisons between baseline and later levels of the dependent variables, and will be conducted with adjusted levels of significance as appropriate (e.g., t-tests with Bonferroni corrections).

Additional analyses will use separate models testing interaction terms to consider whether stable characteristics of the individual (i.e., hostility or defensiveness, general levels of perceived social support, nature of relationship with the support provider) may alter effects of either oxytocin or social support on responses to stress. Population based studies that have looked at the distribution of hostility or defensiveness suggest that there is a broad range of scores that are skewed toward lower levels, even in populations with somewhat higher mean scores [126,127]. Moreover, individuals with high levels of these traits tend to have lower levels of social support [66,126], making it less likely that they would have a close friend and would therefore be excluded from the study initially. As we are randomizing individuals to support or no support, and cell sizes are moderate (n = 40), it is not unreasonable to expect a relatively equal distribution across the conditions of individuals with specific characteristics that might affect responses to the social support manipulation. We will however, control for these individual differences in the primary analyses. Additional analyses will consider effects of individual differences by stratifying across individuals who are high and low in a particular trait and examine for trends that might suggest possible interactions. We will also examine if perceptions of support provided during the experiment are influenced by oxytocin. As the support provided is highly standardized, perceptions of greater support may suggest that oxytocin enhances receptivity to support.

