#### Basic protocol

For eligible participants, sensors and transducers are attached for continuous monitoring of autonomic nervous system activity. Participants are asked to complete baseline questionnaire measures assessing relevant demographics and individual differences. After completing these questionnaires participants have a quiet period during which time they read neutral magazines. Following this "vanilla baseline" resting period (found to be effective in reducing effects of extraneous factors), a baseline measure of autonomic indices and the first saliva sample is obtained [70,71]. Consent for the experimental tasks and videotaping is then obtained, and the study physician subsequently administers a single dose of either 24 IU oxytocin or placebo intranasally (approximately 40 min before stress exposure). Following previous work in this area, a dose of 12 IU is sprayed into each nostril [39,72]. In the highly unlikely event of an adverse reaction during the conduct of the experiment, clear procedures have been set up to protect participants.

Task instructions for the stress tasks are given at this time. The stress tasks are initiated 40 minutes after oxytocin or placebo administration, the amount of time other studies have demonstrated it takes for oxytocin to act in the central nervous system [72]. Immediately prior to performing the task, a state mood measure and a second saliva sample are obtained. State mood and post-task measures and additional saliva samples are obtained after completion of the stress tasks. Autonomic function is monitored throughout the procedure. Prior research has strongly indicated that social-evaluative threat is strongest when an evaluative audience is present and the performance is being captured for permanent record [73]. Thus, video cameras mounted in the ceiling record participants' face and upper body during task preparation and performance. In addition to increasing levels of social-evaluative threat, the videotaping procedure also provides an additional method for assessing whether and how participants' responses to social stress varies across conditions; videotapes may be coded later for emotional responses during task conditions by raters blind to study hypotheses or experimental conditions.

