### Power and Sample Size

Power is calculated to accommodate both the effects of the dichotomous experimental factors, as well as age (measured as a continuous variable). Since power will be limited by hypotheses where 3-way interactions are being tested, power is first computed for representative outcomes for those hypotheses (including vagal tone measured by RSA), based on information available in the existing literature. Power for hypothesis 1 will be higher. Power is calculated for a two-sided test of a three-way interaction over ranges of reliabilities and differences to be detected. For all outcomes, 40 participants per gender/treatment group will result in power of 80-90% to detect effect sizes similar to those seen in the literature. Since participants are used as their own controls, power varies by measurement reliability, and this sensitivity was considered. Power was computed using a normal test that assumes independence across participants, compound symmetric covariance within each subject, and approximately constant variance before and after the treatment. Values for the parameters used here were obtained from the literature [72,88,89,98,128]. In addition, a sample of this size will provide 80% power to detect a medium sized effect using multiple linear regression to consider age and oxytocin adjusting for other covariates as necessary [129].

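### Adjusting for the pre-drug baseline would give more precise oxytocin estimates on autonomic and hormone outcomes at no extra data cost; the planned change comparison is valid but generally less efficient

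*Protocol article*

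**What the plan says.** In the Protocol article, Data Analyses, hypothesis 1 is to be examined "by comparing the change in responses before and after stress across the oxytocin and placebo control groups". Hypotheses 2 to 4 use near-identical wording for the drug-by-support, drug-by-gender and drug-by-age questions. For oxytocin, support and gender the example model is "we will use analyses of variance (ANOVA) with repeated measures". Age is handled by multiple linear regression with an age-by-oxytocin term and covariates that are not listed, with linear mixed models as a possibility. For the physiological measures, the Autonomic Nervous System (ANS) Activation section says that "scores from the baseline condition will be compared with task condition scores to indicate reactivity".

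The order of events is in Basic protocol. After a quiet rest, "a baseline measure of autonomic indices and the first saliva sample is obtained". Only then, once consent for the tasks has been given, "the study physician subsequently administers a single dose of either 24 IU oxytocin or placebo intranasally". Later, "Immediately prior to performing the task, a state mood measure and a second saliva sample are obtained", so that second sample and the first state mood score both follow dosing.

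On adjustment, Data Analyses says: "Analyses will include adjustment for covariates if not covered by randomization". The same section also controls the primary analyses for individual differences such as hostility, defensiveness and perceived support. The baseline value of the outcome is not mentioned as a covariate.

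Power and Sample Size says: "Since participants are used as their own controls, power varies by measurement reliability". It assumes compound symmetry and roughly constant variance, and gives no correlation, standard deviation or effect size.

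**The concern.** With two time points, the group-by-time term of a repeated-measures ANOVA is the test on change scores. A change score fixes the coefficient on baseline at 1, whereas regression estimates it. Under equal variances the best coefficient is ρ, so subtracting the whole baseline adds noise whenever ρ is below 1.

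For the oxytocin contrast nothing is gained by accepting that noise. The drug is randomised and blinded, and the baseline comes before it, so the baseline cannot be affected by treatment. The adjusted and change analyses therefore estimate the same effect.

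The existing adjustment wording does not secure the gain. It is triggered by imbalance between groups, whereas the precision gain from a prognostic baseline is there even when the groups are balanced.

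What is at stake is power for the interaction tests, because the protocol itself says that the three-way interactions limit its power.

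**Working it through.** **Inputs**
- Pre-drug baseline for autonomic and salivary outcomes: yes (Basic protocol).
- Two-sided 5% tests (Data Analyses); 40 participants per gender/treatment group and 80-90% power (Power and Sample Size).
- Compound symmetry and equal variance σ² before and after (Power and Sample Size).
- Baseline-to-task correlation ρ: not given. Assumed 0.5 to 0.8, with 0.3 and 0.9 shown for sensitivity.
- Effect size and SD: not given.

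**Step 1: the plan's own figure.** The 80-90% power can be neither reproduced nor refuted, because its inputs are not stated. What can be shown is the gender × drug × time contrast detectable with change scores:

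SE = σ√(2(1−ρ)) × √(4/m), with m per gender-by-drug cell; detectable effect = (1.96 + 0.84) × SE for 80% power and (1.96 + 1.28) × SE for 90%.

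- m = 40, ρ = 0.5: SE = σ × 1 × 0.316, so 0.886σ to 1.025σ.
- m = 40, ρ = 0.8: SE = σ × 0.632 × 0.316, so 0.560σ to 0.648σ.
- If 40 is instead the size of each gender × drug × support cell, m = 80: 0.626σ to 0.725σ and 0.396σ to 0.458σ.

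**Step 2: adjusted versus change, equal variances.** Per participant:

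- Var(change) = 2σ²(1−ρ)
- Var(baseline-adjusted) = σ²(1−ρ²)
- Ratio = (1−ρ²) / [2(1−ρ)] = (1+ρ)/2

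The variance cut is (1−ρ)/2, the SE cut is 1−√((1+ρ)/2), and the extra participants that a change analysis needs for equal precision are 2/(1+ρ)−1. The last column is the power of the adjusted test where the change-score test has 80%.

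| ρ (assumed) | Variance cut | SE cut | Extra participants | Power |
|---|---|---|---|---|
| 0.3 | 35% | 19.4% | 53.8% | 93.5% |
| 0.5 | 25% | 13.4% | 33.3% | 89.9% |
| 0.6 | 20% | 10.6% | 25.0% | 87.9% |
| 0.7 | 15% | 7.8% | 17.6% | 86.0% |
| 0.8 | 10% | 5.1% | 11.1% | 84.0% |
| 0.9 | 5% | 2.5% | 5.3% | 82.0% |

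**Step 3: simulation check.** With 4,000 replicates and 80 or 160 per drug arm, the simulated variance ratio was 0.745 and 0.754 at ρ = 0.5 (formula 0.75), and 0.914 and 0.909 at ρ = 0.8 (formula 0.90). Estimating the baseline slope costs almost nothing at these sizes.

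**Step 4: unequal variances.** Let k be the task SD divided by the baseline SD. The variance cut is 1 − k²(1−ρ²) / (1 + k² − 2ρk).

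| k | ρ = 0.5 | ρ = 0.7 | ρ = 0.8 |
|---|---|---|---|
| 0.8 | 42.9% | 37.2% | 36.0% |
| 1 | 25% | 15% | 10% |
| 1.25 | 10.7% | 1.9% | 0% |
| 1.5 | 3.6% | 0.2% | 4.7% |

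The gain is never negative, but its size depends heavily on k, which the article only assumes to be about 1.

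**The case against.** The strongest reply is that this is a preference among valid analyses. Under randomisation the change-score contrast is unbiased for the oxytocin effect, and the power section is consistent with it, since participants serve as their own controls there too. That stands. Regression to the mean after a chance baseline imbalance is not a separate defect either: it is the same loss of precision seen in a single trial.

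Second, the wording is flexible. Repeated-measures ANOVA is introduced as an example within the general linear model, and mixed models, several covariance structures and unnamed covariates are allowed. None of this forbids baseline adjustment, and an analysis plan that is not shown may specify it. That also stands in part. What the article does fix is the comparison, which is worded as change for every hypothesis, and its general adjustment rule depends on imbalance.

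Third, a reader might infer several stronger things that the article does not support:
- That a known 10-25% of the information is lost. No correlation is stated, and the figure needs both ρ of 0.5 to 0.8 and equal variances.
- That all four hypotheses go through repeated-measures ANOVA. The age hypothesis is assigned to regression and has its own power statement.
- That age is excluded from the ANOVA models. The article does not say so; it just does not name age there.
- That one baseline-adjusted model serves every outcome and contrast. State mood has no pre-drug value. Support is assigned before the visit (Social Support Manipulation), so the resting baseline follows a known assignment. If support shifts that baseline, the change and adjusted support contrasts estimate different quantities.

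**Conclusion.** The point holds as a free improvement in efficiency for oxytocin contrasts on autonomic and salivary hormone outcomes. It is not an error of validity, and it does not show the stated 80-90% power to be wrong.

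Its size is conditional. Under the protocol's own covariance assumption and an assumed ρ of 0.5 to 0.8, a change analysis needs about 33% to 11% more participants to match the adjusted one, and a test with 80% power would have about 90% to 84%. If the task SD is 1.25 to 1.5 times the baseline SD, the variance gain over the same range of ρ is between 0% and about 11%. If the task SD is 0.8 times the baseline SD, the gain is 36% to 43%. Adjustment is worth specifying because it does not lose in large samples and the interaction tests have the least power to spare.

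**What to change.** State in the analysis section that, for autonomic and salivary hormone outcomes, the oxytocin main effect and the oxytocin-by-gender and oxytocin-by-age interactions will be estimated from a model of the post-drug values:

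- Include the pre-drug baseline of the same outcome as a covariate whether or not the arms look balanced. With several time points, a mixed model with a common baseline mean across drug arms does the same job.
- For hormones, use the first saliva sample as the baseline. The second is taken after dosing and must not be used as a baseline covariate.
- Include age as a prognostic covariate in these models.
- Exclude state mood from this rule, because its first measurement follows dosing.
- For contrasts involving social support, tabulate the resting baseline by support arm and report the change-score analysis alongside the adjusted one.
- State the baseline-to-task correlation and variance ratio assumed in the power calculation, so that the gain can be judged.

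The cost is a change of wording. It needs no new data, visits or participants.

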Research on this topic is limited. Much of the work investigating the effects of oxytocin on physiology and behavior in relation to social connectedness as well as stress has been conducted in animals. In addition to their primary findings, these studies have suggested that oxytocin is more potent in the presence of higher estrogen levels, leading investigators to hypothesize that effects of oxytocin are stronger in females than in males. Serious methodological barriers in assessment and measurement of oxytocin in humans present challenges to working in this area. As a result, relevant empirical evidence for physiological and behavioral effects of oxytocin in human populations is still scarce. Of the studies in humans, many have been conducted in samples of either all men or all women with restricted age ranges. Thus, few of these studies have had the opportunity to consider effects of oxytocin in relation to age, or to compare effects of oxytocin on stress and positive social interaction across men and women. This paper describes an experimental protocol in humans that addresses many of these limitations. The protocol is designed to determine whether oxytocin reduces stress-related neuroendocrine and autonomic activation and subjective distress across age and gender, and to examine the effects of oxytocin in relation to those of social support. To make the relevant comparisons possible, the protocol includes men and women across a broad age range. This protocol also breaks through prior methodological barriers that have made it particularly difficult for U.S. investigators to conduct experimental research with oxytocin in humans, by identifying techniques for using intranasal (exogenously administered) oxytocin in a rigorously controlled laboratory setting with human participants.

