**Figure 1 F1:**
[figure not shown]
**Sample Recruitment Protocol**.

We conduct extensive screening to determine individuals' health status. Initial screening is conducted on the telephone. For this, participants are informed of the nature of the questions to be asked and the anticipated duration of the screening process (up to 20 minutes). Participants are asked a series of questions about age, medication use, health status, health behaviors, and whether they have a same-sex close friend that could come with them to the laboratory, and will be given basic information about the study. Individuals who have **any **known medical condition (including mental disorders) or are taking **any type **of medication (including birth control pills) are excluded. Because overweight individuals may be at excess risk of undetected diabetes or hypertension, individuals with body mass index (BMI) ≥ 30 kg/m^2 ^are excluded. Further exclusions include pregnancy, breastfeeding, smoking, heavy alcohol use, drug use [as assessed by validated instruments, the CAGE and the RAGS, [67,68], or lack of a close friend who could join the participant for the experiment.

If they are still menstruating, all eligible women are asked to participate during the follicular phase of their menstrual cycle. Study outcomes of interest may be influenced by hormonal fluctuations related to the menstrual cycle. Due to variability in the length of menstrual cycles, it is difficult to determine which phase women are in (luteal, ovulation) and their hormone levels. However, when the menstrual cycle begins, it essentially resets the clock for these fluctuations. Thus we can be confident women are in the follicular phase if we examine them within the first 7 days of starting their cycle. Moreover, at this time hormone levels are relatively low and stable; studies that are concerned about effects of these hormones on other physiological processes are often done during this time [69].

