### Future Directions

This research uses a multidisciplinary approach to examine neurobiological underpinnings for the observed epidemiological associations between positive social interactions and emotion experiences and physical health outcomes in older adulthood. Our study will systematically test a biobehavioral model of social relationships and health, and examine a key peptide that may underlie the observed beneficial effects of positive social interactions and psychological states on health and longevity. At conclusion of the study we will have solid evidence concerning the effects of oxytocin on stress response, whether it has similar effects regardless of age or gender, and whether its potency depends in part on circulating levels of estradiol. Further work can build on this knowledge and consider potential effects of oxytocin on other biological parameters such as levels of inflammation or catecholamines.

Future research should examine how effects of oxytocin may relate to effects of different types of social support (friend, same sex, stranger, etc), and whether oxytocin may actually promote provision of more support or greater receptiveness to all kinds of support. A greater understanding of how oxytocin functions in human health may also be obtained by identification of gene by environment interactions in relation to oxytocin, and by considering the relation between oxytocin, the opioid pathway and endogenous opioids.

This novel area of investigation has the potential to have major impact on understanding how positive social and emotional experiences influence adult stress response, health, and longevity. This research will provide a solid platform from which to launch a larger interdisciplinary research program aimed at identifying neurobiological underpinnings for the observed epidemiological associations between positive social interactions and emotion experiences and physical health outcomes in older adulthood. A neurobiological understanding of resilience can inform efforts for both prevention and intervention of diseases or problems common in later life.

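### The pre- versus post-menopausal comparison is largely an age comparison, and the exploratory estrogen analysis is too weak for the article's claim of solid evidence on estradiol

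*Protocol article*

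**What the plan says.** **The analysis.** Data Analyses, hypothesis 3, says: "Exploratory analyses will consider whether the strength of the effects of oxytocin may be attributable to differences in estrogen levels". The first part is "comparing effects of oxytocin across pre- and post-menopausal women (estrogen levels are expected to be higher among pre-menopausal women"). The same sentence adds a second part: "also considering interactions between estrogen (measured directly via levels of estradiol) and oxytocin in both men and women". Hormone Measures confirms that the moderator is observed: "Estrogen is measured using estradiol obtained from the first saliva sample taken at the laboratory session".

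**The testing window.** The Sample section says "all eligible women are asked to participate during the follicular phase of their menstrual cycle", meaning the first 7 days of the cycle. One reason given is that "at this time hormone levels are relatively low and stable".

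**The rationale.** Background reports that animal studies suggest "oxytocin is more potent in the presence of higher estrogen levels". The section on methodological and conceptual challenges names estrogen and aging as alternative reasons why oxytocin's potency might vary.

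**Age in the models.** Age × oxytocin is planned for hypothesis 4. For the estrogen analysis no age term is named. Data Analyses has a general rule to adjust for covariates that randomisation has not balanced, and a strategy that starts from all interactions and simplifies by likelihood ratio tests.

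**The claim.** Future Directions says the study will end with solid evidence on, among other things, "whether its potency depends in part on circulating levels of estradiol". Potential Limitations mentions neither the age link nor the testing window.

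**The concern.** A pre/post-menopausal comparison of the oxytocin effect estimates everything that differs between the two groups and modifies that effect. Age is the obvious rival to estrogen, and hypothesis 4 exists because the investigators think it needs testing. If oxytocin works less well, or better, in older women for reasons unrelated to estrogen, the menopausal comparison will show it, and the plan as written would allow it to be described as an estrogen effect.

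The testing window pulls the other way. It is a defensible way to reduce noise, but it narrows estradiol among menstruating women, and it narrows the pre/post difference on which the first part relies. A null estradiol interaction would then say little about higher estradiol levels. Neither limitation fits with a promise of solid evidence on estradiol.

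**Working it through.** The article gives no figure for the estrogen analysis, so there is none to reproduce. Its stated 80-90% power concerns three-way interactions and cannot be recomputed, because the effect sizes and reliabilities are only attributed to the literature.

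**Inputs from the article.** Ages 25 to 65 (Sample); two-sided 5% tests (Data Analyses); 40 per gender/treatment group (Power and Sample Size). The last gives 2 × 40 = 80 women if treatment means drug only, or 4 × 40 = 160 if it means each drug-by-support cell. Both are shown.

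**Assumptions.** Women's ages are uniform over 25-65, with a sharp menopausal cut at 51 (varied from 45 to 55). Half of each group receives oxytocin. The outcome is a change score with SD 1. The oxytocin effect falls linearly with age by 0.4 or 0.8 SD over the 40 years (0.1 or 0.2 SD per decade), and estrogen plays no part. These slopes are illustrative; nothing in the article supports a particular value.

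**Step 1: how far menopausal status is age.**
- Share post-menopausal: (65 − 51)/40 = 0.35.
- Mean ages: (51 + 65)/2 = 58 and (25 + 51)/2 = 38, a gap of 20 years.
- SD of age: 40/√12 = 11.55.
- Correlation: √(0.35 × 0.65) × 20/11.55 = 0.83.
- Variance inflation: 1/(1 − 0.826²) = 3.1.

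Cuts from 45 to 55 give correlations of 0.87 to 0.75 and variance inflation of 4.0 to 2.3. If age at menopause varies with SD 3-5 years around 48-52, the gap is 18.6-19.5 years and the correlation 0.75-0.82.

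**Step 2: the spurious difference.** Slope × gap = (0.4/40) × 20 = 0.20 SD, or (0.8/40) × 20 = 0.40 SD.

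**Step 3: how often it would be significant.** The standard error is √(4/n_post + 4/n_pre).
- 80 women (28 and 52): √(4/28 + 4/52) = 0.469.
- 160 women (56 and 104): √(4/56 + 4/104) = 0.332.

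The table gives rejection rates for menopause × oxytocin from 10,000 simulated trials per row, with the normal approximation in brackets.

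| Women | Age decline | Unadjusted | Age as main effect | Age and age × oxytocin |
|---|---|---|---|---|
| 80 | 0.4 SD | 7% (7%) | 7% | 5% |
| 80 | 0.8 SD | 13% (14%) | 13% | 5% |
| 160 | 0.4 SD | 9% (9%) | 9% | 5% |
| 160 | 0.8 SD | 22% (23%) | 22% | 5% |

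The mean estimate is about 0.20 or 0.40 SD in the first two models and about zero in the third. An age main effect shifts the outcome level in both arms, so it cannot remove confounding of an interaction.

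**Step 4: the simplification rule.** Suppose the starting model did include age × oxytocin. Beside menopause × oxytocin, that true term reaches p < 0.05 in only 6-9% of trials with 80 women and 7-13% with 160. Simplification by likelihood ratio test would usually drop it.

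**Step 5: the estradiol part.** No estradiol values are given, so the loss of range from early-follicular testing cannot be quantified. Qualitatively, estradiol among women is expected to follow menopausal status and therefore age. In a model pooling men and women it also carries the sex difference.

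**The case against.** The best defence is that the menopausal comparison is only half of the estrogen analysis. The same sentence plans an interaction with directly measured estradiol, and the closing claim is about circulating estradiol, which matches that half. The whole analysis is labelled exploratory. The article separates estrogen from aging, plans an age × oxytocin model for hypothesis 4, and may leave the covariate list to a fuller plan. Hypothesis 4 is also a partial check: with a 0.8 SD decline, a linear age × oxytocin test in the same women would detect it about 18% of the time with 80 women and 31% with 160, more often than the menopausal comparison would mislead.

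Most of this stands, and it limits the point. A reader might infer that the estrogen analysis as a whole cannot inform on estradiol; the measured-estradiol part rules that out. A reader might also infer that women are tested when hormones are lowest, but the article says only that levels are relatively low and stable, so a smaller pre/post difference may remain. Nor does the article say that a null hypothesis 3 would count against estrogen; it uses estradiol to explain a gender difference if one is seen. Nothing in it shows that excluding contraceptive users narrows the contrast.

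Two parts of the defence fail. The general covariate rule does not help, because a main effect leaves the bias intact and age is expected to balance across drug arms anyway. The exploratory label does not support a promise of solid evidence; it makes that promise harder to defend.

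**Conclusion.** The point holds for the menopausal comparison and, more mildly, for the closing claim. The comparison is strongly confounded with age: correlation about 0.8 and a gap of about 20 years, under assumed uniform ages and menopause near 51. An age-only decline of 0.4-0.8 SD would appear as a 0.2-0.4 SD menopausal difference, significant in about 7-13% of trials with 80 women and 9-22% with 160, against a nominal 5%. At the lower slope the excess is small. The error rates depend on the assumed slope; the confounding itself does not.

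The estradiol part is weakened but usable. The size of the weakening cannot be derived from the article. Together the two parts can give exploratory evidence on estradiol, not solid evidence.

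**What to change.** 1. Make the measured-estradiol × oxytocin interaction, which is already planned, the main estrogen analysis. Fit it within sex, or with estradiol centred within sex, with age and age × oxytocin in the same model. Keep age × oxytocin in that model whatever the simplification step suggests.
2. Report the pre/post-menopausal comparison descriptively only, not as evidence about estrogen.
3. Add the early-follicular testing window to Potential Limitations, stating that a null result does not exclude effects at higher estradiol.
4. In Future Directions, replace solid evidence on estradiol dependence with exploratory evidence.

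The cost is some wording and a wider interval for the estrogen interaction. If a menopause term is kept beside age × oxytocin, its variance rises by a factor of about 2.3-4.0. With 160 women and 80% power, the smallest detectable menopausal difference then moves from 0.89-1.02 SD to 1.55-1.77 SD; with 80 women it moves from 1.25-1.45 SD to 2.19-2.51 SD. That width shows how little these data can separate menopause from age. The testing window, recruitment and design stay as they are.
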